## Methods: assignment of interventions

### Randomization and blinding

Randomization is carried out as block randomization using computer-generated random numbers, stratified by center, sex-, and age-specific BMI percentiles at admission (two strata: < 10th percentile vs. ≥ 10th percentile) at a ratio of 1:1 to the two treatment arms. Randomization lists were prepared by the Institute of Medical Informatics and Statistics at Kiel University ([name]. [name]). The randomization sequence is transferred to the participating treatment centers in sequentially numbered, sealed envelopes separately for each center-specific stratum (sex and age- and sex-specific BMI percentiles). Randomization in either the HoT arm of the study or the TAU arm takes place 1 week (± 2 days) before the start of the differential treatment, i.e., at the latest in the 7th week of IP. This time lag is necessary for organizational issues (e.g., parents taking time off from work, communicating with the school). If the patient meets the inclusion criteria for HoT after 4 to 7 weeks of inpatient treatment (and he or she included in the trial), the allocation is determined by having the approved staff at the treatment center open the respective envelope and communicate the news to the patient, family, and treatment team. Blinding of participants or study staff is not possible due to the nature of the treatments. However, a member of the staff who is assigned to another work area and who is not involved in any of the treatments assesses the clinical variables and conducts the interviews. Moreover, the BMI (weight in one’s underwear and height), an objective parameter, is used as the primary endpoint; a staff member who is blinded to the patient’s study arm (single-blind) assesses and records it.

## Methods: data collection, management, and analysis

### Data collection and management

The data management is carried out by the clinical trials center Kiel (ZKS Kiel) at Kiel University. Data collection at the respective centers is carried out with paper case report forms (CRFs) specifically prepared for this study in a pseudonymized manner in accordance with the ICH-GCP guidelines. Each included patient is assigned a numeric identification code to prevent identification. The master file containing the numeric codes and respective patient names will only be stored on paper, which is locked in a safe location with restricted access in the respective sites. This file will be deleted at the latest on May 31, 2035, 10 years after study completion, to fully anonymize the data. One copy of the CRF is sent to the clinical trials center (ZKS Kiel), where it is entered into an “Open Clinica” trial data base via double data entry. Data entry, safety, security, and storage are performed according to local standard operating procedures (SOPs). Standardization procedures, including methods to ensure standardization between sites, are developed and implemented across the sites to guarantee accurate, consistent, complete, and reliable data. In particular, the data collection and documentation are regularly monitored by a qualified monitor of the Clinical Trials Center Aachen (CTC Aachen) in accordance with the GCP guidelines and local SOPs.

### Statistical methods

#### RCT

The superiority of the HoT arm over the TAU arm will be analyzed for the primary endpoint (BMI 1 year after admission) using a linear mixed model for repeated measures in which study arm, sex, BMI at admission and at randomization, and age are included as fixed effects, and center and subject ID are included as random effects. All assessments of BMI after randomization (at discharge and at the 9- and 12-month follow-up timepoints) are considered repeated outcomes (the dependent variable); thus, time point is also included as a fixed effect. The difference between the achieved BMI in both study arms at the 12-month follow-up is the parameter of interest. Re-admissions are considered intercurrent events [62] and are handled depending on the timing of readmission. For patients who were readmitted to IP due to an eating disorder during follow-up and who were still in in- or day-patient treatment at the time of the 12-month follow-up assessment or discharged within the 4 weeks prior, we will use the BMI at readmission instead of that at follow-up to obtain a conservative estimate of their BMI. A subgroup analysis for patients with AAN (admission BMI ≥ 10th percentile) will be performed for the primary outcome. In addition, (serious) adverse events ((S)AEs) are tabulated by study arm and in relation to treatment as assessed by the investigator. No statistical tests will be performed for (S)AEs. Secondary endpoints are investigated with analogous logistic, linear or time-to-event (for time to readmission) models, depending on the type of endpoint.

The statistical evaluation of the RCT is carried out according to the intention-to-treat principle: all randomized study participants are included in the statistical analysis, regardless of whether the treatment was completed. In addition, an analysis only of patients treated in accordance with the protocol—i.e., without relevant protocol violations (per protocol set)—will be performed as a sensitivity analysis for the primary outcome. In general, the mixed model for repeated measures analysis can also be applied if some of the outcome data are missing. Further sensitivity analyses considering missing values will be performed.

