**Methods:**

In this multicenter randomized-controlled trial, home treatment for children and adolescents with AN aged 12 to 18 years is established at 5 major treatment centers for AN in Germany. Approximately 240 patients who are admitted to the hospital for AN will be included in the trial. After a short inpatient somatic stabilization phase (5–8 weeks), patients are randomized to receive either treatment as usual (TAU), in the form of continued inpatient or day patient treatment, or the newly developed home treatment (HoT) (*n* = 82/arm, *n* = 164 in total). There are three assessments throughout treatment (admission, randomization, and discharge), as well as follow-up assessments at 9 and 12 months after admission. The BMI at 12 months after admission (primary outcome) is compared between groups (adjusted for premorbid BMI and admission BMI); secondary outcomes include eating disorder and general psychopathology, the number and duration of psychiatric rehospitalizations, quality of life, motivation for treatment and treatment satisfaction. Other secondary outcomes include the primary caregivers’ burden and skills in handling the child’s illness and direct treatment costs. Statistical analysis will be based on intention-to-treat principles, using mixed models for repeated measures. (Serious) adverse events are assessed throughout treatment. In addition, the feasibility and implementation of HoT as well as the satisfaction and workload of the members of the multidisciplinary treatment teams in both arms will be assessed.

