##### Primary outcome

The primary outcome is the BMI (kg/m^2^) 12 months after hospital admission, which is assessed by staff blinded to the treatment allocation. The BMI is the most relevant indicator of long-term treatment success in adolescents with AN and has been used as the primary endpoint in many treatment studies [28, 56, 57]. BMI is calculated for all assessment time points from the measured height and weight of the patient in his or her underwear (except for self-reported values at T4, the interview via phone). Age- and sex-specific percentiles, SDS and %Expected Body Weight (%EBW) are calculated based on the large German reference dataset from the KIGGS study [58]. Recent studies have demonstrated that BMI alone might not be a meaningful prognostic indicator of a good long-term outcome in AAN [59]. Since randomization is stratified for BMI at admission (percentile < 10 vs. ≥ 10) and statistical analyses will be adjusted for BMI at admission and premorbid BMI, we still consider the increase in BMI to be a valid primary endpoint.

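### The abstract and the outcome section promise adjustment for premorbid BMI, but the primary model in the statistical methods does not list it

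*Protocol article*

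**What the plan says.** Three places in the protocol article describe the adjustment of the primary analysis.

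- **Abstract, Methods.** The 12-month BMI "is compared between groups (adjusted for premorbid BMI and admission BMI".
- **Outcomes, Primary outcome.** After conceding that BMI alone may be a poor guide to long-term outcome in atypical AN, the section cites stratification on the admission percentile and continues: "statistical analyses will be adjusted for BMI at admission and premorbid BMI, we still consider the increase in BMI to be a valid primary endpoint".
- **Statistical methods, RCT.** The linear mixed model is itemized: "study arm, sex, BMI at admission and at randomization, and age are included as fixed effects"; "center and subject ID are included as random effects"; and, because the post-randomization BMI values are repeated outcomes, "thus, time point is also included as a fixed effect". Premorbid BMI is not in the list.

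Randomization and blinding says that allocation is "stratified by center, sex-, and age-specific BMI percentiles at admission", with two percentile strata cut at the 10th percentile. The model has no term for that stratum, although it contains admission BMI, age, sex and center.

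**The concern.** Premorbid BMI (before the illness) and BMI at randomization (after several weeks of inpatient stabilization) are different variables, so the difference is not one of wording. An itemized model that lacks a covariate promised twice elsewhere leaves two readings of the primary test. Whichever is used, the analysis departs from something already published, and in an open-label trial that choice should not remain open. The ambiguity can spread, because the secondary endpoints and the cost comparison are to use models analogous to this one.

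The missing covariate also carries part of an argument. The Primary outcome section answers the doubt about atypical AN with three supports: stratification, admission BMI and premorbid BMI. Premorbid BMI is the one that describes the patient's own pre-illness weight. The section on the inpatient stabilization phase says that pre-illness weight is considered when the target weight is set, with emphasis on atypical AN, and Treatment completion ties the end of treatment in both arms to that target. It is therefore plausible, on the plan's own account, that premorbid BMI predicts 12-month BMI.

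**Working it through.** **Step 1. Covariates side by side**

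| Term | Abstract | Primary outcome | Statistical methods, RCT |
|---|---|---|---|
| Admission BMI | yes | yes | yes |
| Premorbid BMI | yes | yes | **no** |
| BMI at randomization | not mentioned | not mentioned | yes |
| Sex, age, time point | not mentioned | not mentioned | yes (fixed) |
| Center, subject | not mentioned | not mentioned | yes (random) |

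The first two places are short and need not be complete, so terms that appear only in the third column are no conflict. Premorbid BMI is a conflict: two places promise it and the itemized list lacks it.

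**Step 2. Supports for the endpoint in atypical AN**

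- Stratification on admission percentile: present in the randomization.
- Adjustment for admission BMI: present in the model.
- Adjustment for premorbid BMI: absent from the model.

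One of the three is missing.

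**Step 3. Possible precision gain**

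Reference point: the sample size section states d = 0.47, 80% power, a 5% level and 74 evaluable patients per arm. Taken as two-sided, 2 × (1.960 + 0.842)² / 0.47² = 71.1, so 72 per arm; the t-test version gives 72.04, so 73. Both are within two patients of 74. Power at 74 per arm is 81.1%.

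Let r be the partial correlation of premorbid BMI with 12-month BMI, given the other covariates. The article gives no value, so r is assumed over a range. Residual variance is multiplied by 1 − r², the equivalent gain on 164 randomized patients is 164 × (1/(1 − r²) − 1), and the effective d becomes 0.47/√(1 − r²).

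| r (assumed) | Residual variance | Equivalent extra patients | Power at 74 per arm |
|---|---|---|---|
| 0.2 | 0.96 (−4%) | 6.8 | 82.6% |
| 0.3 | 0.91 (−9%) | 16.2 | 84.5% |
| 0.4 | 0.84 (−16%) | 31.2 | 87.3% |

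At r = 0.1 the variance falls by 1% and power is 81.4%. These are two-sample approximations to the mixed model and take d = 0.47 as stated.

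**Step 4. The percentile stratum**

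A simulation with assumed values (148 patients; admission BMI, sex and age in the model; a true step between strata of 0, 0.5 or 1.0 kg/m²) compared the treatment-effect estimate without and with the stratum term. Empirical standard errors were 0.263 and 0.263, 0.268 and 0.267, and 0.266 and 0.265. Type I error was 4.3% to 5.5% across both models. The term changes almost nothing once its components are in the model.

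**The case against.** The strongest reply is that this is a drafting slip with little consequence. Leaving a prognostic covariate out of a linear model does not bias a randomized comparison. The predictive value of premorbid BMI beyond admission BMI, randomization BMI, age and sex is unknown: pre-illness weight is only one consideration in setting the target, alongside a usual percentile range and gonadotropin levels. At r = 0.1 to 0.2 power moves only from 81.1% to between 81.4% and 82.6%. The contradiction could also be removed by withdrawing the promise in the abstract and the outcome section, and the article does not say which statement is intended. All of this stands. It limits the consequence but leaves the contradiction in place.

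A reader might infer more than the article supports:

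- **That the safeguard for atypical AN is absent altogether.** It is not. Stratification and admission BMI remain, and a subgroup analysis of the primary outcome is planned with the same 10th-percentile cut as the randomization.
- **That the abstract also rests the endpoint on this adjustment.** It only states the adjustment; the justification is given in the Primary outcome section alone.
- **That omitting the stratum indicator is a material error.** Admission BMI, age, sex and center already carry nearly all of its information, as Step 4 shows.
- **That the covariate is needed to rescue power.** Whether the planned size is adequate is a separate question, and nothing here depends on it.

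**Conclusion.** The point holds in a limited form. The primary analysis is specified in two ways with respect to premorbid BMI, and one of the three supports offered for BMI as the endpoint in atypical AN is missing from the itemized model. This follows from the text alone and needs no assumption.

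The consequence is an ambiguous pre-specification and a rationale that does not match the analysis; there is no bias. Any gain in precision (residual variance lower by 4%, 9% or 16%) depends on assumed partial correlations of 0.2, 0.3 or 0.4 and could be smaller. The point deserves correction before analysis but does not put the trial's conclusions at risk. The statistical analysis plan is not at hand; if it already names premorbid BMI, only the article's model description is out of step.

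**What to change.** Before any unblinded analysis, add premorbid BMI as a fixed effect to the primary model under Statistical methods (RCT). State where the value comes from and how missing values are handled: a simple baseline imputation that uses neither arm nor outcome, so that every randomized patient stays in the analysis. Then make the abstract, the Primary outcome section and the statistical methods give the same covariate list.

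Optionally, add the <10th / ≥10th percentile randomization stratum to align the model with the design; its expected effect is negligible.

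The cost is a change of wording in the protocol and the analysis plan, and one further model parameter. The small downside is that some premorbid BMI values may be missing and will have to be imputed.

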### Interventions

Treatment is provided in a multimodal, interdisciplinary setting. Psychotherapeutic interventions are provided according to the principles of CBT-E (Enhanced Cognitive Behavioral Therapy for Adolescents with Anorexia nervosa) [53], including family-based interventions (family sessions and family meals) encouraging parents to take the lead in refeeding their child [54]. The general treatment goals of AN-focused child and adolescent psychiatric and psychotherapeutic treatment in all participating departments during the intervention phases are depicted in Table 2. The same treatment approaches are provided during all phases of therapy, i.e., during IP before randomization and in both treatment arms (TAU and HoT) after randomization until discharge.

**Table 2 Tab2:** AN treatment goals

General treatment goals	Specific treatment goals		
• weight rehabilitation • identification and reduction of eating disorder-specific cognitions and behaviors • normalization of eating behaviors • reduction of excessive exercise • improvement of distorted body image • guidance of parents/caregivers • reintegration into an age-appropriate everyday life • treatment of comorbid disorders	Inpatient stabilization (5–8 weeks)	HoT (12–16 weeks)	TAU (no length specified)
	• somatic stabilization • development of therapeutic relationship (patients/parents and staff) • psychoeducation (patients & parents) • instruction of parents to chaperone the meals and daily activities of the child (amount of food & extent of physical activity)	• treatment at home to achieve general treatment goals Special focus: • first 2 months: supporting parents as “co-therapists” (refeed child; support during food intake & ED-related behaviors) • third and fourth months: supporting patients in reintegration into an age-appropriate everyday life (e.g., regular school visits, social integration)	• continuation of IP/DP treatment to achieve general treatment goals • if possible, transfer to DP

Abbr.: *AN* anorexia nervosa, *HoT* home treatment, *TAU* treatment as usual, *ED* eating disorder, *DP* day patient treatment

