### Treatment completion

HoT and TAU are continued until the target weight is achieved and sustained, and cognitive, affective, and behavioral symptoms are alleviated. On average, a treatment period of 12 to 16 weeks for HoT was calculated. During the somatic stabilization phase and the treatment in either study arm (TAU, HoT), participants only receive treatment from the staff of the respective treatment site. Additional psychiatric and/or psychotherapeutic treatment is not allowed.

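### The printed primary model has no arm-by-time term, so its arm effect is pooled over discharge, 9 and 12 months and matches the stated 12-month difference only if the effect is constant

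*Protocol article*

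**What the plan says.** The protocol article (Statistical methods, RCT) describes a linear mixed model for repeated measures and names its terms. The first list reads "study arm, sex, BMI at admission and at randomization, and age are included as fixed effects". For the random part, the article gives center and patient identifier. The outcomes are the BMI values after randomization, "at discharge and at the 9- and 12-month follow-up timepoints", and "thus, time point is also included as a fixed effect". No arm-by-time interaction is mentioned there or elsewhere in the article.

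The next sentence sets the target: "The difference between the achieved BMI in both study arms at the 12-month follow-up is the parameter of interest".

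Three other places bear on whether the arm effect could be the same at all three visits:

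- Treatment completion: "HoT and TAU are continued until the target weight is achieved and sustained".
- Table 2 (Interventions): HoT lasts 12 to 16 weeks, while TAU has no set length.
- Primary outcome: BMI comes from measured height and weight, "except for self-reported values at T4, the interview via phone".

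**The concern.** A model with arm and time point as separate main effects has one arm coefficient, common to all visits. The stated parameter belongs to a single visit. Someone who programmed the printed list exactly would report a pooled effect as the 12-month result.

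The two quantities agree if the arm effect does not change from discharge to month 12. Several features of the design speak against relying on that:

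- Both arms are treated toward target weight before discharge, which tends to bring them together at that visit.
- Discharge can fall at a different time since admission in each arm, because TAU is open-ended.
- The 9-month value is self-reported by phone, whereas the 12-month value is measured by blinded staff. The pooled effect gives both the same weight.
- The Introduction and Conclusions argue for HoT partly through fewer relapses after discharge, which suggests a difference that grows over follow-up.

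The error can run either way. A benefit that builds after discharge would be diluted. An early benefit that is gone by month 12 could be reported as a 12-month benefit.

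**Working it through.** **The plan's own figure.** Sample size and recruitment gives 74 evaluable patients per arm for d = 0.47, 80% power and a 5% level. The two-sided normal formula gives 72 and the t version 73; power at 74 is 0.82 or 0.81. The figure is therefore reproduced within two patients, and it concerns a single 12-month comparison.

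**Inputs from the document.** 74 per arm. Expected BMI gains are 3.0 (SD 1.8) and 3.6 (SD 1.5), a difference of 0.6. The root-mean-square SD is √((1.8² + 1.5²)/2) = 1.657. The SD implied by d = 0.47 is 0.6/0.47 = 1.277. Both SDs are used below, because the choice changes the power level but not the comparison.

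**Assumptions, not in the document.** The arm effects at discharge, 9 and 12 months; a common within-patient correlation ρ of 0.5 to 0.85; one SD at all visits; complete data; subject ID read as a random intercept.

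**Estimate.** Arm does not vary within a patient, so with complete data its coefficient is the difference between arms in patient means:

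estimate = (d₃ + d₄ + d₅)/3, for any ρ.

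For 0/0.3/0.6 this is 0.9/3 = 0.30. For 0.6/0.3/0 it is also 0.30, although the 12-month difference is 0.

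**Standard errors.**

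- Pooled effect: SD × √[(2/n)(1 + 2ρ)/3]. At SD 1.657 and ρ = 0.5: 1.657 × √(0.02703 × 0.6667) = 0.222.
- 12-month contrast: SD × √(2/n) = 1.657 × 0.1644 = 0.272.

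**Probability of a significant result in favour of HoT:** Φ(estimate/SE − 1.96). For 0/0.3/0.6 at ρ = 0.5 this is Φ(0.30/0.222 − 1.96) = 0.27. For the 12-month contrast it is Φ(0.60/0.272 − 1.96) = 0.60.

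| Assumed effects (discharge/9/12 mo) | Pooled estimate | SD 1.657: pooled, ρ 0.5/0.7/0.85 | SD 1.657: 12-mo contrast | SD 1.277: pooled, ρ 0.5/0.7/0.85 | SD 1.277: 12-mo contrast |
|---|---|---|---|---|---|
| 0.6/0.6/0.6 | 0.60 | 0.77/0.69/0.64 | 0.60 | 0.94/0.89/0.85 | 0.82 |
| 0/0.3/0.6 | 0.30 | 0.27/0.23/0.21 | 0.60 | 0.42/0.36/0.33 | 0.82 |
| 0/0/0.6 | 0.20 | 0.14/0.13/0.12 | 0.60 | 0.21/0.19/0.17 | 0.82 |
| 0.9/0.75/0.6 | 0.75 | 0.92/0.87/0.83 | 0.60 | 0.99/0.98/0.97 | 0.82 |
| 0.6/0.3/0 | 0.30 | 0.27/0.23/0.21 | 0.025 | 0.42/0.36/0.33 | 0.025 |

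**Checks by simulation.**

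- 74 per arm, SD 1.66, visit correlations 0.4 to 0.7, complete data, 6000 replicates. Effects 0/0.3/0.6 gave an estimate of 0.30 and power of about 25%, against 59% for the 12-month contrast. Effects 0.6/0.3/0 gave about 24% rejection in favour of HoT.
- 82 per arm, SD 1.277, ρ = 0.7, 10% missing at 12 months, 150 runs. Effects 0/0.3/0.6 gave 0.285 (power 0.39) from the printed terms and 0.610 (power 0.82) with the interaction. With missing visits the pooled effect becomes a weighted mean, but the gap hardly changes.

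**The case against.** The strongest reply is that silence is not exclusion. The article does not say main effects only. It calls the analysis a mixed model for repeated measures and names a visit-specific parameter, which suggests that a visit-specific contrast may be intended. The analysis plan, not shown here, may contain the interaction. This stands as a limit: a reader might infer that the investigators have chosen the wrong estimand, and the text does not support that. It does not remove the point. The article goes into detail on covariates and random effects and explains why time enters, yet the one term that ties the model to its target is absent.

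A reader might also infer that the 12-month difference cannot be obtained from this model. That is too strong. Under a constant effect, the pooled coefficient is the 12-month difference and is estimated more precisely.

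Nor is constancy disproved. HoT has a planned length, the Limitations call the phase time frames fixed, discharge also depends on symptoms, and target weights are individual. Convergence at discharge is plausible, not certain.

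A further tempting step is to say that the subject random effect forces equal variance at all visits and so makes the 12-month standard error too small. The article states no residual structure and gives no SD by visit, so the documents do not support this. Covariance structure, degrees of freedom and an admission-BMI-by-time term belong to the analysis plan and are not part of this point.

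**Conclusion.** The point holds for the model as printed. Its terms yield one arm effect pooled over three visits, while the stated target is the effect at the last of them. They coincide only under a constancy assumption that is neither stated nor justified, and that the article's own design makes doubtful.

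The algebra rests on a random subject intercept and complete data. Another residual structure or missing visits would change the weights, but there would still be one pooled effect.

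The size rests on assumed effect profiles and correlations. If the effect grows from 0 to 0.6, the estimate is halved to 0.30 and power is about 25% instead of 59% at SD 1.66 (33 to 42% instead of 82% at SD 1.277). If it fades from 0.6 to 0, a 12-month benefit that does not exist is declared about 25% of the time at SD 1.66. The 59% is below the planned 80% because SD 1.66 exceeds the SD implied by d = 0.47; that is a separate matter. The direction of the bias in this trial is unknown.

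**What to change.** Add the arm-by-time-point interaction, with time point categorical, to the listed fixed effects. State that the primary test is the arm contrast at 12 months from that model. If the interaction is already intended, correct the published list to show it, and check that the analysis plan agrees before the data are analysed.

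This takes one sentence and changes nothing in data collection. The discharge and 9-month values stay in the model and still help with missing 12-month data. The interaction does not cure the uneven timing of discharge, but the 12-month contrast no longer averages over that visit.

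The cost is some power if the effect really is constant: from 0.64–0.77 to 0.60 at SD 1.66, or from 0.85–0.94 to 0.82 at SD 1.277, over the correlations assumed above.
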